##### Post–session–Technical

These measures will be used to assess the feasibility of the video consulting intervention.

*VC Session Evaluation—Client* (project specific measure—video consulting only) relevant items were selected from the patient session review measure from the Agency of Clinical Innovation (ACI) telehealth guidelines (Freedland et al., 2011) and are included along with two items evaluating the picture and sound quality of the video link.

*VC Session Evaluation—Therapist* (project specific measure—video consulting only), has the same items as the client version but with more detail about the quality of the video link. It will be used to assess the quality of each session from the therapist's perspective and record any video or audio dropouts. A schedule of measure administration is provided in Table 3.

**Table 3 T3:** SPIRIT schedule of enrolment, interventions, and assessments for ACT-adjust.

			**Study period**								
			**Enrolment**	**Allocation**	**Post-allocation**						
					**Intervention**				**Evaluation**		
Time Points			T1	T1a	T1b	Weeks 1–7	Week 9	Week 13	T2	T3	T4
					VC training	Session 1–7	Session 8	Session 9			
Enrolment		Eligibility screen	X								
		Informed consent	X								
		Randomization		X							
Interventions		ACT-Adjust FtF									
		ACT-Adjust VC			X						
		Wait list Control									
Assessments	Baseline measures	Demographic data	X								
		RBANS	X								
	Primary Outcome measures	DASS-21	X			X^2^	X^2^	X^2^	X	X	X
		AAQ-ABI	X			X^2^	X^2^	X^2^	X	X	X
	Secondary Outcome measures	QOLIBRI	X						X	X	X
		SLP	X						X	X	X
		ELS	X						X	X	X
		SWLS	X						X	X	X
	Other measures	HTRS^1^				X^2, 3^	X^2, 3^	X^2, 3^			
		SRS V.3				X^3^	X^3^	X^3^			
		VCSE-Client				X^3^	X^3^	X^3^			
		VCSE-Therapist				X^3^	X^3^	X^3^			

1 *Items 1-2 administered at end of the session and Item 3 at the beginning of the following of session*;

2 *Measure administered at the beginning of the treatment session*;

3 *Measure administered at the conclusion of the treatment session. AAQ-ABI, acceptance and action questionnaire-acquired brain injury; DASS-21, depression anxiety stress scales −21; ELS, enhanced living scale; HTRS, home task rating scale; QOLIBRI, quality of life after brain injury; RBANS, repeatable battery for the assessment of neuropsychological status; SWSL, satisfaction with life scale; SRS V.3, session rating scale version 3; VCSE, video consulting session evaluation*.

### Sample Size and Power Calculations

Based on a previous pilot RCT of the ACT-Adjust program (Whiting et al., 2020), sample size calculations on the primary outcome measure (AAQ-ABI) indicate a total sample size of 56 (ES Partial η^2^ = 0.17, Power = 0.80), is required to establish a significant interaction effect from pre to post intervention. A previous RCT for a psychological intervention conducted at the Liverpool Hospital, Brain Injury Rehabilitation Unit screened *n* = 90 participants with *n* = 17 meeting study criteria and agreeing to participate in the trial (Simpson et al., 2011). Using this ratio, it is anticipated ~*n* = 297 participants will need to be screened to recruit the required sample for the current trial.

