## Abstract

**Background:** People with traumatic brain injury (TBI) face a range of mental health challenges during the adjustment process post-injury, but access to treatment can be difficult, particularly for those who live in regional and remote regions. eHealth provides the potential to improve access to evidence-based psychological therapy for people with a severe TBI. The aim of the current study is to assess the efficacy of a psychological intervention delivered via video consulting to reduce psychological distress in people with TBI.

**Methods:** This paper outlines the protocol for a multi-center, three-arm, parallel, non-inferiority randomized controlled trial (RCT) of an evidence-based manualized psychological intervention, ACT-Adjust. ACT-Adjust provides nine sessions for adults with a moderate to severe TBI experiencing clinical levels of psychological distress. Fifty-six participants referred from Brain Injury Rehabilitation Units across New South Wales (NSW) and the NSW icare scheme will be randomly allocated to three conditions; (1) video consulting (VC), (2) face-to-face (FtF) and, (3) a waitlist control (WL).

**Discussion:** This is the first RCT to evaluate the efficacy of a psychological therapy (ACT-Adjust) delivered via video consulting for individuals with a moderate to severe TBI.

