To date, there is no research looking at the efficacy of psychological therapy to treat mental health issues delivered by video consulting to adults with a moderate to severe TBI. The purpose of this paper is to describe the design of a non-inferiority, randomized controlled trial, to examine whether an eHealth-based delivery of the ACT-Adjust treatment program achieves the same treatment effects as face-to-face delivery. It also will examine the efficacy of ACT-Adjust when compared to a wait-list control group and determine whether treatment gains are sustained three months after the intervention.

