**Figure 1 F1:**
[figure not shown]
Study flow diagram.

This paper describes the study protocol (Dated September 30, 2019; Protocol Version 1.0) to comply with the Standard Protocol Items: Recommendations for Interventional Trials (SPIRIT) (Chan et al., 2013), see Supplementary Table 1 for Spirit Checklist. The trial will be conducted according to the Consolidated Standards of Reporting Trials (CONSORT) of Electronic and Mobile HEalth Applications and onLine TeleHealth (CONSORT E-HEALTH) statement (Eysenbach, 2011), CONSORT Social and Psychological Interventions (CONSORT-SPI) (Montgomery et al., 2018) guidelines and CONSORT extension for the reporting of non-inferiority trials (Piaggio et al., 2012). The trial has been registered on the Australian New Zealand Clinical Trials Registry (ANZCTRN2619001602112). Refer to Appendix I for more details.

The study will commence immediately following ethics approval and recruitment of participants will continue for ~2 years. The overall duration of the study will be 3 years to allow for those in the wait list control condition to complete the intervention and the follow up assessment, and for data analysis and dissemination of results. To test the efficacy of the intervention, the study will test the following hypotheses:

ACT-Adjust intervention: Participants in the active treatment regardless of delivery (FtF vs. VC) will demonstrate increased psychological flexibility and decreased psychological distress following the intervention, compared to those in the control group (waitlist).eHealth: There will be no differences in primary and secondary outcomes between participants who receive the ACT-Adjust intervention by FtF compared to those who receive it via VC.Sustained treatment effects: Participants in the active treatment condition, ACT-Adjust (VC and FtF), will maintain their gains three months post intervention.

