### Randomization

The randomization process was performed by a researcher independent of the research team. A computer generated randomization list was generated for each phase of the study using online randomization software, Sealed Envelope (Sealed Envelope Ltd, 2019). The initial randomization had a ratio of 2:3:2 (FtF:WL:VC), with a permuted block size of seven. Following Time 2 Data Collection (13 weeks after Baseline/Time 1), wait list control participants will be randomized to the ACT-Adjust intervention on a ratio of 1:1 (FtF:VC), using a permuted block size of four. The results for both phases were placed in sequentially numbered opaque and sealed envelopes. Following completion of a participant's baseline assessment, the Research Assistant will open the next sequential randomized envelope available to determine the participant's assigned condition. The following allocations are required: ACT-Adjust face-to-face *n* = 16 participants; ACT-Adjust eHealth *n* = 16 participants; Waitlist control *n* = 24 participants.

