### Potential Strengths of the Study

The study has been designed to meet the CONSORT guidelines for non-inferiority trials, psychosocial interventions and eHealth delivery (Eysenbach, 2011; Piaggio et al., 2012; Montgomery et al., 2018). It builds on a previously published RCT using an adaptation of the ACT-Adjust program which indicated statistically and clinically significant reductions in depression and stress but with a smaller sample size (Whiting et al., 2020). The project is a multi-site study to enable recruitment across a wide geographical area and will recruit individuals living across the state of NSW, Australia. The ACT-Adjust intervention will be delivered by clinicians (e.g. clinical psychologists, social workers, etc.) with experience in both ACT and TBI.

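### The trial is declared non-inferiority for video (VC) against face-to-face (FtF), but 56 was sized only for a difference test and the VC–FtF hypothesis is worded as absence of difference

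*Protocol article*

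**What the plan says.** The title, the Abstract and the Overview of Study Design and Research Hypotheses all call the trial non-inferiority. The Introduction gives the purpose as "to examine whether an eHealth-based delivery of the ACT-Adjust treatment program achieves the same treatment effects as face-to-face delivery". Data Analysis places the non-inferiority assessment of the two modes at the 3-month follow-up, and Potential Strengths of the Study states: "The study has been designed to meet the CONSORT guidelines for non-inferiority trials".

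The hypothesis for this comparison (hypothesis 2, eHealth, in the Overview) is: "There will be no differences in primary and secondary outcomes between participants who receive the ACT-Adjust intervention by FtF compared to those who receive it" by VC.

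Sample Size and Power Calculations contains one calculation. Drawing on the earlier pilot RCT, "sample size calculations on the primary outcome measure (AAQ-ABI) indicate a total sample size of 56", with partial eta-squared 0.17 and power 0.80. This number "is required to establish a significant interaction effect from pre to post intervention".

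Randomization allocates 16 to FtF, 16 to VC and 24 to the wait list. After Time 2, "wait list control participants will be randomized to the ACT-Adjust intervention on a ratio of 1:1 (FtF:VC"). Data Analysis does not say whether these 24 enter the VC–FtF comparison.

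**The concern.** Three stated elements do not fit together: a non-inferiority design, a sample size for detecting a difference, and a hypothesis of no difference. The planning effect comes from a pilot that compared ACT-Adjust with an active control (Introduction), so it is not a VC–FtF contrast. It also refers to the pre-to-post change, whereas non-inferiority is to be assessed at 3 months.

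A prediction of no difference is a null hypothesis. Failing to reject it shows only that the data did not resolve a difference, and this happens more often the smaller the trial. Non-inferiority needs a confidence bound that excludes a stated margin. The Discussion expects the results to bear on access to therapy for people in remote and regional areas, so how a VC–FtF result may be read matters.

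**Working it through.** **Inputs from the protocol.** Partial eta-squared 0.17, power 0.80, total 56; arms 16/16/24; wait list re-randomized 1:1, giving at most 16 + 12 = 28 per mode.

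**Assumptions, because the text gives no figure.** Two-sided 5% for the difference test; one-sided 2.5% for non-inferiority, with 5% as the alternative; SD = 1, meaning the SD of the analysed change score; no dropout; true VC–FtF difference 0 for non-inferiority power.

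**Step 1: planning effect.** f = √(0.17/0.83) = 0.453. If it came from a two-group comparison, d = 2f = 0.905 SD.

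**Step 2: reproducing 56.** Comparing one active arm with the wait list at a 2:3 ratio, the normal approximation for d = 0.905 at two-sided 5% gives 16 v 24 with power 0.801, and 16 + 24 + 16 = 56. The protocol does not say this was the route. Alternatives also land nearby: a three-group test on change scores gives 51 (57 after allowing 10% dropout), or 53 under another convention for the noncentrality, which becomes 56 when rounded up to whole blocks of seven. Every route found that reaches about 56 tests for a difference; none uses a margin.

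**Step 3: what 56 gives for VC v FtF.** With n per mode, SE = √(2/n) and df = 2n − 2. The 95% half-width is t(0.975, df) × SE:
- n = 16: 2.042 × 0.354 = 0.72 SD
- n = 28: 2.005 × 0.267 = 0.54 SD

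Non-inferiority power for margin M is P(T > t(1 − α, df)), with T noncentral t and noncentrality M/SE. The probability of a non-significant result when VC is worse by δ is P(|T| < t(0.975, df)), with noncentrality δ/SE.

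| | 16 per mode | 28 per mode |
|---|---|---|
| Smallest margin with 80% power, one-sided 2.5% | 1.02 SD | 0.76 SD |
| Same, one-sided 5% | 0.90 SD | 0.67 SD |
| Power at an illustrative margin of half the planning effect (0.453 SD), one-sided 2.5% | 24% | 38% |
| Non-significant if VC loses half the planning effect (δ = 0.453) | 76% | 62% |
| Non-significant if VC loses all of it (δ = 0.905) | 30% | 9% |

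An 80% chance at the illustrative 0.453 SD margin would need 78 per mode at one-sided 2.5%.

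**Step 4: does baseline adjustment rescue it?** At a margin of 0.5 SD of the follow-up score, one-sided 2.5%, with an assumed baseline–follow-up correlation of 0.5 to 0.7, power is about 35–48% with 16 per mode and 56–73% with 28. It stays below 80%.

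**The case against.** Four points can be made for the protocol.

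*The comparison may not be 16 v 16.* Hypothesis 2 speaks of those who receive the intervention by each mode, which can include re-randomized wait-list participants. The 1:1 second randomization, the 3-year duration that lets them finish treatment and follow-up, and the T4 column in Table 3 all suggest that they may count. This stands: a reader might infer a 16 v 16 test, but the document fixes neither 16 nor 28, so both are shown.

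*Nothing says non-significance will be read as non-inferiority.* A reader might infer that VC can pass through imprecision alone. That follows only if hypothesis 2 is judged by a non-significant test. Data Analysis speaks of assessing non-inferiority, and the protocol adopts the CONSORT non-inferiority extension. With a margin and a confidence bound, imprecision would make VC fail instead. The margin itself may sit in an analysis plan not shown here, so its absence is not the fault. What remains is the hypothesis as worded and an N that no choice of analysis population or reasonable margin is shown to support.

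*Some margins below the planning effect are attainable.* It is tempting to say that none is. That fails at one-sided 5% with 16 per mode (0.90 v 0.905 SD), with 28 per mode, and with adjustment for baseline at an assumed correlation of 0.5 (about 0.89 change-score SD with 16 per mode at one-sided 2.5%).

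*This is phase II, and VC v FtF is not the only aim.* True: hypothesis 1 compares ACT-Adjust with the wait list, and the difference-test sizing suits that question. But phase II status supports calling the VC–FtF comparison estimation; it does not support the confirmatory label.

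**Conclusion.** The point holds as a contradiction in what the protocol states. The sample size of 56 is justified for a difference test only, and hypothesis 2 is worded so that no result could establish it. The consequence depends on how that hypothesis is judged:

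- **By non-significance:** a VC format losing half the planning effect would appear no different about 76% (16 per mode) or 62% (28) of the time.
- **By a margin and confidence bound:** at one-sided 2.5%, any margin below 0.76 SD has less than 80% power even with all 56 participants. Success becomes less likely than not once the margin falls below roughly the half-width, 0.54 SD with 28 per mode or 0.72 SD with 16.

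These figures rest on an unadjusted comparison, no dropout and the alpha levels shown; the non-inferiority figures also assume no true difference. The 0.905 SD benchmark assumes a two-group source. Baseline adjustment improves the figures without changing the conclusion for margins near 0.5 SD. The documents do not support saying that the trial will wrongly declare VC as good as FtF, only that its stated size and hypothesis do not serve the declared aim.

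**What to change.** 1. In Sample Size and Power Calculations, state that 56 is justified only for the interaction (difference) test and does not power VC–FtF non-inferiority. Describe the VC–FtF comparison as phase II estimation, and align the title, the Overview of Study Design, Data Analysis and Potential Strengths of the Study.
2. Replace the no-difference wording of hypothesis 2 with the VC-minus-FtF difference and its confidence interval, read against a margin that the investigators pre-state and justify. Add that a non-significant difference will not be taken as non-inferiority.
3. State that the VC–FtF comparison uses both randomizations (up to 28 v 28), with time counted from the start of ACT-Adjust and randomization phase as a covariate. Define T4, which appears only in Table 3, for wait-list starters.

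The cost is a less ambitious claim and slightly more analysis work. No extra patients or visits are needed, since Table 3 already schedules the outcome measures at T2, T3 and T4.

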### Informed Consent

During the consent process, all participants will be informed as to the purpose of the research, any potential risks or benefits and processes to withdraw from the study and provided with the Participant Information Sheet (see Supplementary File 2). By definition, clients who have the cognitive capacity to participate in the ACT-Adjust program, will have sufficient cognitive capacity to provide written informed consent. Participants' capacity to provide informed consent will be determined by a review of any available neuropsychological assessment and in consultation with their treating health professionals including their Rehabilitation Specialist. Consent will be fully explained to the participants in simple language and they will be given the opportunity to have a family member present during the consent process. Language will be used at an appropriate level for participants' cognitive impairment and extra time will be provided for participants to process and think about the research. All consent for the trial will be undertaken by the Chief Investigator (DW).

### Blinding

Psychologists conducting baseline assessments (Time 1) will be blinded to participant treatment allocation, as participants will be randomized after the baseline assessment (Time 1). Blinding of the treating psychologists providing the intervention is not possible, however an independent assessor will be used to complete the post-treatment (Time 2) and 3-month follow-up assessments (Time 3) and will be blinded to the condition. The success of blinding will be assessed by having the independent assessor (i) indicate which condition they think the participant was randomized to (FtF, WL or VC) and (ii) indicate if the participant disclosed their treatment condition. Data analysis will be undertaken by a statistician, from the Ingham Institute for Applied Medical Research but not directly associated with the individual research group, who will be blinded to the treatment conditions. It is not anticipated unblinding will be required for the independent assessor or statistician and therefore is not permissible in this study.

### Data Analysis

Data will be entered into SPSS statistics software (IBM Corp, 2019), reviewed for missing data and then screened for normality on all outcome measures and for each treatment group. Prior to the main analysis, between groups comparisons will be undertaken to test for equivalency of the groups using chi-square and *t*-tests. Where participants withdraw or are not contactable for the follow up assessment, the last recorded measures will be carried forward to remaining assessment points for data analysis. Primary analysis will be implemented on an Intention-to-Treat basis, using hierarchical linear mixed models to study the differential effects of each treatment condition. For the post-treatment analyses between the three treatment conditions, analysis will focus on linear time effects, treatment conditions and interactions. Cohen's effect size will be calculated for all analyses. Analyses will focus on the estimated mean differences relative to pre-treatment levels on primary and secondary outcome measures (see Table 3). For the longer-term treatment effects, the non-inferiority of the face-to-face and video consulting will be assessed at the 3-month follow-up.

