The shortened session times (~60 min) is proposed to assist in reducing fatigue and improving attentional processes for participants with cognitive impairments. The additional relapse prevention session (Session 9), aims to improve sustainability of treatment gains which were not achieved in the original ACT-Adjust clinical trial (Whiting et al., 2020). Metaphors were substituted to be VC compatible and more concrete (e.g., Chinese Finger Trap) enhancing participants' comprehension of the session focus. Further strategies to compensate for participants' cognitive impairments and fatigue after TBI translated from the original ACT-Adjust trial, included reviewing and repeating session material at the beginning of the following session, and provision of a hardcopy of the participant workbook printed in size 14 font, with a Flesch Readability Ease rating of 76.4 and Flesch-Kincaid Grade Level of 4.8. In addition, the therapist facilitates completion of workbook exercises, and session specific text message reminders are provided to facilitate completion of between-session home tasks, and for fatigue management, sessions were scheduled at a time favored by the participant, breaks were provided if required and sessions rescheduled if participants felt unable to attend. A summary of the program content is available in Table 1. The intervention will be delivered throughout New South Wales, Australia, by authors DW, MM, and JW and other trained mental health professionals recruited to the project, using the ACT-Adjust 2.0 Therapist Manual.

**Table 1 T1:** Summary of the ACT-Adjust 2.0 program.

**Session no**.	**Content**
1	**Confronting the Agenda** Introduction to the program—Guidelines and boundaries, reasons to see the psychologist, aims of ACT-Adjust, program outline Administer measures Exercise: Mindfulness activity (Mindfulness of the breath, 2 min) Confronting the agenda—identifying individual issues, workability, breathing, mindfulness exercise Home task—Introduce concept of home tasks, reasons for home tasks and home task contract, home task rating sheet Conclusion—Brief summary of the session

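### Last observation carried forward is applied before a mixed model that does not need it; it enters zero relapse for anyone missing at 3 months and can distort the video versus face-to-face comparison

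*Protocol article*

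**What the plan says.** The Data Analysis section of the protocol article sets one missing-data rule: where participants withdraw or cannot be reached, "the last recorded measures will be carried forward to remaining assessment points for data analysis". The next sentence reads "Primary analysis will be implemented on an Intention-to-Treat basis, using hierarchical linear mixed models". The same section states that "the non-inferiority of the face-to-face and video consulting will be assessed at the 3-month follow-up". It describes no other missing-data method and no sensitivity analysis.

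Three other places bear on this:

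- **Hypotheses** (Overview of Study Design and Research Hypotheses). The third hypothesis is that participants in the active arms "will maintain their gains three months post intervention". The second begins "There will be no differences in primary and secondary outcomes between participants who receive the ACT-Adjust intervention by FtF" and compares them with those treated by video.
- **Earlier evidence** (Intervention: ACT-Adjust 2.0). The added relapse-prevention session "aims to improve sustainability of treatment gains which were not achieved in the original ACT-Adjust clinical trial".
- **Session scores.** DASS-21 and AAQ-ABI are taken at the start of every therapy session. The Session Measures section describes these as clinical, Table 3 lists them in the primary-outcome rows, and Appendix I defines the primary outcomes at baseline, end of therapy and 3 months only. Wait-list participants have only a baseline score before Time 2.

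**The concern.** A likelihood-based mixed model takes each participant's available assessments and is valid if missingness depends only on data in the model. Carrying scores forward first gives up that property: the model receives filled-in values as if they had been observed.

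The filled-in value also answers one of the trial's questions. Hypothesis 3 asks whether gains hold from Time 2 to Time 3, and the rule records that they held for everyone not seen at Time 3. The protocol itself reports that gains were not sustained in the earlier trial, so some loss after therapy is plausible. Non-inferiority is judged at the same time point, where carried-forward values accumulate. There, a shrunken difference makes a false claim of non-inferiority more likely.

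**Working it through.** The plan gives no figure to reproduce here: no expected dropout, no margin and no relapse rate. The sample size of 56 is not used. Assumptions, for illustration only: 10–30% missing, margin 0.5 SD, one-sided 2.5% test, change-score SD 1, Time 2–Time 3 correlation 0.6. From the Randomization section there are 16 per active arm, or 16 + 24/2 = 28 if the re-randomised wait-list participants are added.

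**1. Maintenance.** Let d be the share seen at Time 2 but missing at Time 3. Let L_obs and L_mis be the mean losses from Time 2 to Time 3 in those seen and those missing.

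- True loss = (1 − d)·L_obs + d·L_mis.
- Loss after carrying forward = (1 − d)·L_obs + d·0.
- Understatement = d·L_mis, which is positive whenever the missing participants lost some gain on average.
- If missingness is unrelated to relapse, L_obs = L_mis = L and the apparent loss is (1 − d)·L. With L equal to half the gain, it is 0.9 × 0.50 = 0.45, 0.8 × 0.50 = 0.40 and 0.7 × 0.50 = 0.35 at 10, 20 and 30% missing.

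**2. Video versus face-to-face at Time 3, equal loss after Time 2.** Let D2 and D3 be the true shortfalls of video at Times 2 and 3. The estimate is (1 − d)·D3 + d·D2.

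| D2 | D3 | d | Estimate | Effect |
|---|---|---|---|---|
| 0 | 0.50 | 0.2 | 0.8 × 0.50 = 0.40 | shrinks |
| 0 | 0.50 | 0.3 | 0.7 × 0.50 = 0.35 | shrinks |
| 0.50 | 0.50 | 0.2 | 0.40 + 0.10 = 0.50 | none |
| 0.50 | 0.25 | 0.2 | 0.20 + 0.10 = 0.30 | widens |

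False non-inferiority was simulated with D3 equal to the margin and data missing completely at random at Time 3:

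| Per arm | d | D2 = 0, carried forward | D2 = 0.5, carried forward | Observed data only |
|---|---|---|---|---|
| 16 | 0.2 | 4.6% | about 2.5% | about 2.5% |
| 16 | 0.3 | 6.1% | about 2.5% | about 2.5% |
| 28 | 0.2 | 5.6% | about 2.5% | about 2.5% |
| 28 | 0.3 | 7.7% | about 2.5% | about 2.5% |

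Repeated runs agree to within about 0.3 percentage points.

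**3. Unequal dropout, baseline carried forward.** Take a face-to-face gain of 0.9 and a video gain of 0.4, so the true difference is 0.50.

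- Video 30%, face-to-face 10% lost: 0.9 × 0.9 − 0.7 × 0.4 = 0.81 − 0.28 = 0.53 (conservative).
- Video 10%, face-to-face 30% lost: 0.7 × 0.9 − 0.9 × 0.4 = 0.63 − 0.36 = 0.27 (anti-conservative).
- No true difference (both gain 0.9), video 30%, face-to-face 10%: 0.81 − 0.63 = 0.18, a deficit for video that does not exist.

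**4. Active versus wait list at Time 2.** Take an active gain of 0.9 and a wait-list change of 0.3 (true difference 0.60), with 20% lost in each arm. Wait-list dropouts can carry only baseline, giving 0.8 × 0.3 = 0.24. Active dropouts carry a fraction p of the gain, giving 0.9 × (0.8 + 0.2p).

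- p = 0 (session scores do not count): 0.72 − 0.24 = 0.48.
- p = 0.5 (mid-therapy score): 0.81 − 0.24 = 0.57.
- p = 0.8 (late score): 0.864 − 0.24 = 0.624.

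**The case against.** The strongest reply is that direction and size depend on a dropout pattern nobody yet knows. That is right for the between-arm comparisons, and several stronger readings that a reader might infer are not supported:

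- *The rule always shrinks the video versus face-to-face difference.* It does not. The difference is unchanged if it is stable from Time 2 to Time 3, and widens if it narrows after Time 2 or, in the example above, if video loses more participants.
- *The active arms certainly carry mid-therapy scores taken by the unblinded therapist.* The text does not settle whether session scores count as last recorded. If they do not, everyone lost before Time 2 carries baseline in every arm. The secondary outcomes have no session scores in any arm. Both primary measures are self-report, which limits the force of the blinding point.
- *The rule inflates the effect against wait list.* Of the three equal-dropout cases above, only the late-score case does so. The Treatment Conditions section also removes participants with persistent extremely severe DASS-21 scores. Carrying such scores forward would work against the active arms.
- *Standard errors are always too small.* This has not been shown as a general result.

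It could also be said that a journal article condenses the plan. But this is a stated rule, not an omitted detail. The maintenance point survives all of this: the imputed change is zero whatever the dropout pattern.

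**Conclusion.** The rule should go. For participants seen at Time 2 and missing at Time 3 it sets relapse to zero, which favours hypothesis 3 whenever those participants lost any gain on average. Under missingness unrelated to relapse, the apparent loss is 90 to 70% of the true loss at an assumed 10–30% missing. This needs no assumption about margin or arm size.

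For non-inferiority the claim is narrower: the rule can shrink or distort the difference. The inflated error rates in the working hold for a shortfall that emerges after Time 2 and an assumed 0.5 SD margin. Different dropout patterns give no bias or a conservative one. A method whose bias turns on unknown dropout is a poor basis for a non-inferiority claim, even though its sign cannot be stated in advance.

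Unequal treatment of active and wait-list arms is conditional on session scores counting as last recorded. The protocol needs to say whether they do; the direction of any resulting bias depends on the dropout pattern.

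**What to change.** 1. Delete the carry-forward sentence. State that the mixed model is fitted to all observed scheduled assessments without imputation, under missing-at-random.
2. State that session DASS-21 and AAQ-ABI scores are not substituted for Time 2 or Time 3 outcomes.
3. Deal with removals under Treatment Conditions. These depend on session DASS-21 scores, so a model that ignores those scores may not meet missing-at-random for these participants. Either let the session scores inform the missing-data model, for example as auxiliary variables in multiple imputation, or treat these removals explicitly in a sensitivity analysis.
4. Add a missing-not-at-random sensitivity analysis that shifts missing post-treatment values by a stated delta, varied by arm.

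The cost is a few sentences, slightly wider intervals and a little more analysis work. Nothing further is collected from participants.
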